#### **4.1 Inclusion Criteria**

Patients eligible for inclusion in this trial must meet **all** of the following criteria:

1. Patient's written informed consent has been obtained
2. Primary diagnosis of Major Depression/MD (single-episode or recurrent) according to the Structured Clinical Interview for DSM-5 (SCID-5-CV; also ICD-10 coded - assessment not older than 14 days on the day of randomisation request)
3. A score of  $\geq 17$  on the 24-item version of the Hamilton Rating Scale for Depression (HRSD-24) - assessment not older than 14 days on the day of randomisation request
4. A total score of at least 15 on the Occupational Depression Inventory (ODI) - assessment not older than 14 days on the day of randomisation request
5. Sick leave related to depressive or burn-out complaints for at least 7 days during the last 12 months
6. Sufficient German language skills
7. Outpatient status
8. 18-years or older
9. Patients must have a regular work activity that is expected to continue for at least 6 months at the time of randomisation.

#### **4.2 Exclusion Criteria**

Patients eligible for this trial must **not** meet any of the following criteria:

1. Acute risk of suicide
2. History of psychotic symptoms, bipolar disorder, or organic brain disorders
3. A primary diagnosis of another SCID-5-CV disorder
4. Concurrent diagnosis of substance dependency
5. Antisocial, schizotypal, or borderline personality disorder (SCID-5-PD)
6. Other ongoing psychotherapy
7. Antidepressive pharmacotherapy (if not stable for at least the last 4 weeks before randomisation)
8. Serious medical condition or time restrictions interfering with participation in regular sessions
9. Current sick leave > 4 weeks
10. Applying for rehabilitation or early retirement
11. Patient without legal capacity who is unable to understand the nature, significance and consequences of the study
12. Simultaneous participation in other studies which could interfere with this study and/or participation before the end of a required restriction period. No prior randomisation in this IPT-Work trial.

13. Persons who are in a disciplinary employment relationship with a member of the study team

## **5 Procedures**

The study procedures for all patients comprise the stages of screening (see 5.1), consent (see 12.1), randomisation (see 5.2), treatment (see 5.3.2 for intervention arm, 5.3.3 for control arm, 5.3.1 for both arms) and follow-up (see 5.4), which are described in detail below. The visit schedule (Table 5) provides a compact overview of the processes for each patient.

Table 5: Visit Schedule

| Trial Period                                                                   | Baseline             |                    | Treatment   |             |             |             |             |             | Post-treatment | Follow-up/ End of Trial |
|--------------------------------------------------------------------------------|----------------------|--------------------|-------------|-------------|-------------|-------------|-------------|-------------|----------------|-------------------------|
|                                                                                | Screening
14 days | Randomi-
sation | 8 weeks     |             |             |             |             |             | 13 weeks       |                         |
| Visits                                                                         | V0                   | V1                 | V2          | V3          | V4          | V5          | V6-
V10  | V11         | V12            | V13                     |
| Week                                                                           |                      | W0                 | W1          |             | W2          |             | W3-7        | W8          | W9             | W21                     |
| Time Window                                                                    | day -14 -
day 0   | day 0              | ± 4
days | ± 4
days | ± 7
days | ± 7
days | ± 7
days | ± 7
days | ± 7 days       | ± 7 days                |
| Informed Consent                                                               | x                    |                    |             |             |             |             |             |             |                |                         |
| Inclusion/Exclusion Criteria                                                   | x                    |                    |             |             |             |             |             |             |                |                         |
| Demographics Medical History                                                   | x                    |                    |             |             |             |             |             |             |                |                         |
| Work Context                                                                   | x                    |                    |             |             |             |             |             |             | x              | x                       |
| Structured Clinical Interview for DSM-5 (SCID-5)**                             | x                    |                    |             |             |             |             |             |             |                |                         |
| Hamilton Rating Scale for Depression (HRSD-24)                                 | x                    |                    |             |             |             |             |             |             | x              | x                       |
| Occupational Depression Inventory (ODI)*                                       | x                    |                    |             |             |             |             |             |             | x              | x                       |
| Days of sick leave*                                                            | x                    |                    |             |             |             |             |             |             | x              | x                       |
| Confirmation of SCID-5, HRSD-24, ODI
(if older than 14 days: re-assessment) |                      | x                  |             |             |             |             |             |             |                |                         |
| Beck Depression Inventory II (BDI-II)*                                         | x                    |                    |             |             |             |             |             |             | x              | x                       |
| Work Ability Index (WAI)*                                                      | x                    |                    |             |             |             |             |             |             | x              | x                       |
| Return to Work Attitude (RTW-SE)*                                              | x                    |                    |             |             |             |             |             |             | x              | x                       |
| Effort-Reward-Imbalance (ERI) at work*                                         | x                    |                    |             |             |             |             |             |             | x              | x                       |
| Job Content Questionnaire 2 (JCQ2)*                                            | x                    |                    |             |             |             |             |             |             | x              | x                       |
| WHOQOL-BREF (Quality of Life)*                                                 | x                    |                    |             |             |             |             |             |             | x              | x                       |
| Connor-Davidson Resilience Scale (CD-RISC)*                                    | x                    |                    |             |             |             |             |             |             | x              | x                       |
| Patient treatment preference*                                                  | x                    |                    |             |             |             |             |             |             | x              |                         |
| Randomisation**                                                                |                      | x                  |             |             |             |             |             |             |                |                         |
| Individual preliminary talk (see 5.3.1)**                                      |                      |                    | x           |             |             |             |             |             |                |                         |
| Treatment IPT-Work vs SP sessions**                                            |                      |                    | x           | x           | x           | x           | x           | x           |                |                         |
| Therapeutic element checklist (Stundenbogen)**                                 |                      |                    | x           | x           | x           | x           | x           | x           |                |                         |
| Change of medication/therapy**                                                 |                      |                    |             |             |             |             |             |             | x              | x                       |
| Adverse Events / Serious Adverse Events**                                      |                      |                    | x           | x           | x           | x           | x           | x           | x              | x                       |

\*Self-rated by patient \*\* After informed consent

## 5.1 Patient screening for eligibility

If a patient appears to be eligible for the trial (see 4.1 and 4.2 for inclusion and exclusion criteria), a rater will inform the patient about the trial and ask the patient for his/her written consent, and will assess the patient's eligibility. It is imperative that written consent is obtained prior to SCID-5, which is a trial-specific procedure. The rater will inform the patient that a group of 4-6 eligible patients has to be collected before the entire group will be randomised to the IPT-Work or SP condition and, if necessary, will check the eligibility criteria once more directly before randomisation.

The rater will then record the details of these trial patients on the following trial-specific lists:

- **Subject screening log:** for the documentation of trial patients who were checked for eligibility before and/or during the clinical trial. The following will be entered:
  - consecutive screening number (1, 2, 3 etc.),
  - date of written consent (if obtained),
  - details on whether the patient was randomised,
  - if not randomised, the reason.
  - For all patients who signed informed consent, the individual patient identification code (see below) will be recorded on the subject screening log.
- **Subject identification log:** A confidential log of
  - the names of all trial patients
  - the patient identification code assigned to each patient (see below).

With this list, the identity of each patient can be revealed. The list must be kept confidential and remain at the trial site. It must not be copied or otherwise be passed on! However, sponsor representatives, clinical research associates (CRAs), auditors and representatives of authorities must be allowed to inspect the list on request.

- **Patient identification code:** A unique trial-specific identification number which identifies the patient and consists of two parts: The first three digits correspond to the site number, the next one or two digits stand for the number of the patient according to the Subject screening log. For example 987-2 (Site No. 987, patient No. 2), so that each patient with consent is numbered uniquely across the entire database.

All patients who have signed the informed consent form will be entered into the trial database.

Patients who have signed the informed consent form but are not randomised between treatments are called screening failures. The reason(s) for screening failure will be documented in the trial database, and their numbers will be given in the respective box in the CONSORT diagram.

For these patients (screening failures), at least the following data will be recorded:

- Date of informed consent
- eCRF pages on fulfilment of eligibility criteria
- Demography data, Medical history, Work context, data about sick leave
- SCID-5, ODI and HRSD-24
- Patient will be randomised between IPT-Work and SP. If a patient is not randomised, a reason (eligibility criteria which are not fulfilled, wish of patient, other: specify) is given.

All randomised patients and their treatment and follow-up data will be documented in the trial database. Further details see Chapter 8.

## **5.2 Patient randomisation**

In this trial groups of 4-6 eligible patients at a time will be cluster-randomised to the IPT-Work or SP condition. When a group of patients is ready for randomisation, the rater will check that SCID-5, HRSD-24 and ODI are not older than 14 days at the day of randomisation request and that all data required for randomisation (see 5.1) are available in the eCRF.

The other data for V1 according to the Visit Schedule (see page 28) must be recorded on paper before randomisation. They should be entered to the trial database within 14 days from randomisation.

After data entry for 4-6 patients, the rater hands over the completed Randomisation Request Form to the study psychotherapist who checks the request, signs and forwards the request to the CTU Freiburg (for contact details see chapter Responsibilities) for randomisation. Forwarding the “Randomisation Request Form” occurs either per FAX or e-mail upon availability at the site. The Randomisation Team at the CTU Freiburg processes the request and returns the randomisation result to the designated persons at the site using FAX or e-mail. The study psychotherapist enters the results into the eCRF.

To maintain the blinding, access to the randomisation module in the eCRF is restricted to the sites study therapist. The same must be ensured for the e-mail or fax reply confirming the randomisation results.

While the blank “Randomisation Request Forms” are filed in the ISF, the returned completed “Randomisation Request Forms” have to be kept at the site in the “Randomisierungs- und Therapiegruppenordner” in a secured place.

The Randomisation Team at the CTU Freiburg processes the Randomisation Request according to the CTU instructions. The Data Management at the CTU confirms the entry of the results. The completed “Randomisation Request Form” is kept at the CTU in a secured place.

Information about each randomisation (without the assignment to one of the arms) is automatically communicated to the Coordinating Investigator, the Principal Investigator at the site concerned and the central Data Management at the CTU. The study psychotherapists will not disclose the randomisation result, nor any information on ongoing or previous IPT-Work or SP psychotherapy groups at his/her centre to the raters involved in patient recruitment and follow-up. The team at the centre keep their personnel who enters data which might reveal the patients’ treatment allocation under strict duty of confidentiality.

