### **3.4 Methods against bias**

For logistical reasons, clusters of 4-6 eligible patients at a time will be randomised to group psychotherapy according to the IPT-Work or SP condition. To avoid selection bias, the raters who identify eligible patients and obtain informed consent will not be informed about the randomisation result, nor about ongoing or previous IPT-Work or SP psychotherapy groups at their respective centre.

To further avoid selection bias, the randomisation code to allocate patient groups to interventions will be generated by the CTU using the following procedure to ensure that treatment assignment is unbiased and concealed from patients and site staff. Randomisation of patient groups will be performed, stratified by centre, in blocks of variable length with a 1:1 ratio. The block lengths will be documented separately and will not be disclosed to the centres. The randomisation code will be produced by validated programmes based on the Statistical Analysis System (SAS).

Obviously, blinding of patients and study psychotherapists performing the interventions is not possible. However, data acquisition other than patient reported outcomes will be done by trained blinded clinical raters not involved in patient management. Each site will implement procedures to mask patient treatment assignment from the clinical rater by reminding the patients at each visit not to mention anything that might reveal their treatment condition. Diagnostic training of raters in the SCID-5, HRSD-24 and (S)AE assessments will be conducted by expert trainers and interrater reliability will be ensured. The other measures are self-rated in a standardised questionnaire format.

All confirmatory analyses are fully specified in the trial protocol to avoid reporting bias. The trial is registered prospectively at the German Clinical Trials Register (see chapter 13), and its results will be published irrespective of the outcome to prevent publication bias.

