### **3.5.4 Psychotherapists**

Study psychotherapists are in a completed or far advanced stage of psychotherapy training. All therapists will execute IPT-Work as well as SP groups after thorough training to ensure a high treatment quality (2-day training course in presence in each IPT-Work and SP followed by 3 half-day online booster workshops after the start of the group therapies app. every 6 months). All trainings are led by clinical experts in the field ([name], [name], [name], [name], [name] or others delegated by the CI). Study therapists will be intensely instructed and trained to adhere to the manual of each condition and not to mix the intervention types. To check for adherence and to support the supervision, a 'Therapeutic Element Checklist' (Stundenbogen) for IPT-Work (e.g. strategies for addressing work-life-balance, demand-control-balance, effort-reward-balance, and work as a social role) and SP (e.g. reflective listening, facilitation of affect, helping the patient to feel understood) is filled out by the therapist immediately after each group session. Separate supervisors ([name], [name] or others delegated by the CI) for each treatment arm will review the 'Therapeutic Element Checklist' regularly in ongoing supervision. Every second or third session will be supervised by the responsible supervisors (who also conducted the IPT-Work and SP trainings, respectively) in biweekly video conference meetings. Furthermore, a diagnostic training of raters in SCID-5 and HRSD-24 will be conducted in presence ([name], [name], [name] or others delegated by the CI), and interrater reliability will be ensured.

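### Concealment is weakened, though not lost, at the last step before allocation: the request is checked and sent by a therapist who very likely knows the centre's earlier allocations

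*Protocol*

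**What the plan says.** Section 3.4 (Methods against bias) gives two safeguards against selection bias. First, "the raters who identify eligible patients and obtain informed consent will not be informed about the randomisation result", nor about groups running or completed at their centre. Second, the CTU generates the allocation code by a procedure intended "to ensure that treatment assignment is unbiased and concealed from patients and site staff". Whole groups are randomised 1:1, stratified by centre, in blocks of variable length that the centres are not told.

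Section 5.2 (Patient randomisation) describes the route. The rater checks that the diagnostic interview, HRSD-24 and ODI are no more than 14 days old, sees that the data for 4-6 patients are entered, and completes the request form. The rater then "hands over the completed Randomisation Request Form to the study psychotherapist who checks the request, signs and forwards the request to the CTU Freiburg". The CTU assigns the arm and replies to designated persons at the site. "The study psychotherapist enters the results into the eCRF", and "access to the randomisation module in the eCRF is restricted to the sites study therapist"; the e-mail or fax reply is to be protected in the same way.

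Two further statements show what therapists can be expected to know. Section 3.5.4 says "All therapists will execute IPT-Work as well as SP groups". Section 5.2 forbids the therapist to pass on the result, "nor any information on ongoing or previous IPT-Work or SP psychotherapy groups at his/her centre to the raters involved in patient recruitment and follow-up".

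**The concern.** The protocol itself treats knowledge of earlier groups at a centre as a selection risk before allocation, which is why raters are shielded from it. Yet the last site person to act before the CTU assigns the arm is the one most exposed to that knowledge. A check followed by a signature implies some discretion to withhold or return a form. Section 5.2 does not say what the check covers, and it neither grants nor excludes holding the form back.

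Such discretion could matter in three ways. Group size may be 4, 5 or 6. The 14-day validity of the entry assessments is counted to the day of the request, so a delay can force re-assessment under the visit schedule (Table 5), and a patient may then miss an entry threshold. A patient who is not randomised can be recorded with a free-text reason (section 5.1). If the expected arm influenced any of these, the arms could differ in who enters them before treatment starts. The primary model adjusts for baseline HRSD-24 only, and so would not remove differences in other respects.

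**Working it through.** **Step 1: who knows what before allocation.**

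| Role | Task before allocation | Knowledge of earlier groups |
|---|---|---|
| Rater | identifies, consents and assesses patients, completes the form | shielded (3.4, 5.2) |
| Study psychotherapist | checks, signs and forwards the form | not shielded: enters results, has sole site access to the randomisation module, delivers both arms (3.5.4, 5.2) |
| CTU | assigns the arm after the request arrives | holds the list (3.4, 5.2) |

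That the therapist knows earlier allocations is a strong inference, not a stated fact. The duty not to tell raters about earlier groups would be empty otherwise.

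**Step 2: groups per centre.** Inputs: 144 patients (3.3), groups of 4-6 (3.4), 6 centres (3.2).

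- Groups of 6: 144/6 = 24, and 24/6 = 4 per centre.
- Groups of 5: 144/5 = 28.8, and 28.8/6 = 4.8 per centre.
- Groups of 4: 144/4 = 36, and 36/6 = 6 per centre.

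This assumes equal recruitment across the 6 centres.

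**Step 3: chance of guessing the next arm.** The protocol states no figure to reproduce and does not give the block lengths, so the lengths are assumed and a range is shown. Lengths are counted in groups, and each length in a set is taken as equally likely. For each position k in the centre's sequence:

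P(correct at k) = sum over histories h of P(h) × max{P(A | h), P(B | h)}

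This is averaged over the K positions in a centre.

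Worked example, lengths 2 or 4, K = 4:

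- Position 1: 0.5.
- Position 2: guess the other arm. ½ × 1 + ½ × 2/3 = 0.833.
- Position 3: the history is balanced with probability ½ + ½ × 2/3 = 5/6 (chance 0.5) and unbalanced with probability 1/6 (then certain). 5/6 × 0.5 + 1/6 × 1 = 0.583.
- Position 4: ½ × 1 + ½ × 0.833 = 0.917.
- Mean: (0.5 + 0.833 + 0.583 + 0.917)/4 = 0.708.
- Certain to someone who knows the set of lengths: probability 1/6 at position 3 and 1/6 at position 4, so (1/6 + 1/6)/4 = 0.083.

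Exact enumeration for the other cases:

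| Assumed lengths | Correct, K = 4 / 5 / 6 | Certain, K = 4 / 5 / 6 |
|---|---|---|
| 2, 4 | 70.8% / 67.5% / 70.8% | 8.3% / 8.3% / 8.3% |
| 2, 4, 6 | 66.6% / 65.2% / 68.6% | 0.8% / 2.0% / 3.0% |
| 4, 6 | 65.4% / 64.3% / 67.2% | 1.3% / 5.0% / 7.5% |

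In every row the simple rule of guessing the arm used less often so far at the centre, and tossing a coin when balanced, does exactly as well. The guesser therefore needs the centre's history but not the block lengths.

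**The case against.** The strongest reply is that the core of concealment is intact. The CTU generates and holds the list, varies and withholds the block lengths, and assigns only after receiving the request, so the therapist does not know the next arm when forwarding. The group has been recruited, consented and assessed by shielded raters, and the form is complete at handover. Every consenting patient enters the screening log and the database, with a reason if not randomised (5.1), so removing a patient would leave a trace. Therapists deliver both arms, so no motive for steering is evident. All of this stands and limits the weight of the point. It does not close the gap: the undisclosed variable lengths are already built into the figures above, and a trace of a dropped patient does not show a delayed or returned request.

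It may also be objected that making the rater the sender brings the blinded assessor of the primary endpoint closer to the allocation correspondence. The existing rule in section 5.2, which restricts the reply to the therapist, answers this, provided that the reply address is one the rater cannot read.

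A reader might infer several stronger things that the documents do not support:

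- That concealment fails at allocation. Better-than-chance guessing is not knowledge.
- That group membership is still open when the therapist receives the form. The handover follows data entry for the whole group.
- That one therapist knows every earlier group. A centre may have several therapists.
- That the next arm can be guessed up to 75% of the time. That figure needs fixed blocks of 2, which contradicts the variable lengths in section 3.4.

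**Conclusion.** The point holds as a weakness in the procedure. The wish in section 3.4 to keep knowledge of earlier groups away from whoever could influence selection is not carried through to the last step in section 5.2. For a person who knows the centre's history, the next arm is guessable about 64-71% of the time instead of 50%, with about 1-8% of allocations certain. This rests on three assumptions: mixed block lengths of 2/4, 2/4/6 or 4/6; about 4-6 groups per centre; and a therapist who knows the earlier allocations there.

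The percentages measure predictability, not bias. No effect on group composition, on the treatment estimate or on the type I error has been shown. It is a cheap improvement, not a flaw that undermines the trial.

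**What to change.** In section 5.2 and on the request form, for groups still to be randomised: the rater, who is unaware of earlier groups, closes the group list and sends the completed request directly to the CTU. The CTU replies only to the therapist, as the section already requires.

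If the therapist's signature is to stay, state that the list is locked at handover, and that the check is formal and cannot alter the membership, size or timing of the group.

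The principal investigator is a less suitable sender. Section 5.2 says "Information about each randomisation (without the assignment to one of the arms) is automatically communicated to the Coordinating Investigator, the Principal Investigator" and others, but nothing states that the principal investigator is unaware of earlier groups.

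The cost is a change of routing in one section and one form. Two practical conditions follow: therapist availability must be confirmed before the list is closed, and the reply must go to a therapist-only address so that the raters stay blinded.
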